## Abstract

**Introduction:**

Atrial fibrillation (AF) is a major cardiovascular health problem: it is common, chronic and incurs substantial healthcare expenditure because of stroke. Oral anticoagulation reduces the risk of thromboembolic stroke in those at higher risk; but for a number of patients, stroke is the first manifestation of undetected AF. There is a rationale for the early diagnosis of AF, before the first complication occurs, but population-based screening is not recommended. Previous prediction models have been limited by their data sources and methodologies. An accurate model that uses existing routinely collected data is needed to inform clinicians of patient-level risk of AF, inform national screening policy and highlight predictors that may be amenable to primary prevention.

**Methods and analysis:**

We will investigate the application of a range of deep learning techniques, including an adapted convolutional neural network, recurrent neural network and Transformer, on routinely collected primary care data to create a personalised model predicting the risk of new-onset AF over a range of time periods. The Clinical Practice Research Datalink (CPRD)-GOLD dataset will be used for derivation, and the CPRD-AURUM dataset will be used for external geographical validation. Both comprise a sizeable representative population and are linked at patient-level to secondary care databases. The performance of the deep learning models will be compared against classic machine learning and traditional statistical predictive modelling methods. We will only use risk factors accessible in primary care and endow the model with the ability to update risk prediction as it is presented with new data, to make the model more useful in clinical practice.

**Ethics and dissemination:**

Permissions for CPRD-GOLD and CPRD-AURUM datasets were obtained from CPRD (ref no: 19_076). The CPRD ethical approval committee approved the study. The results will be submitted as a research paper for publication to a peer-reviewed journal and presented at peer-reviewed conferences.

**Trial registration details:**

A systematic review to incorporate within the overall project was registered on PROSPERO (registration number CRD42021245093). The study was registered on ClinicalTrials.gov (NCT04657900).

Strengths and limitations of this studyLarge and nationwide dataset representative of the UK primary care population.Using artificial intelligence technology may discover new predictive variables by efficiently incorporating temporal information of event data.The model will not just predict the risk of a patient developing atrial fibrillation, but also provide a representation of how risk develops over time to enable more focused screening.The derivation and validation work will be undertaken in datasets collected over the same time period in the UK; therefore, further validation work may be pursued with newly collected data and for international contexts.The derivation data will not include unstructured natural language free text; future research could explore if incorporating free text into representation learning improves predictive accuracy.

## Introduction

Atrial fibrillation (AF) is the most common sustained cardiac arrhythmia. The current estimated prevalence is between 2% and 4%, and a 2.3-fold rise is expected due to extended longevity in the general population.^1^ While AF may present with symptomatic palpitations, for many patients, the first diagnosis of AF is only after they present with stroke or cardiac decompensation. The frequency of AF in ischaemic strokes is 20%–30%, and these are usually severe, resulting in permanent disability or fatality.^2^

Oral anticoagulants can reduce the risk of stroke by up to two-thirds in those with AF at higher risk of stroke.^3^ International guidelines recommend that patients with AF at elevated thromboembolic risk are offered stroke prophylaxis with an oral anticoagulant.^1^ Most patients with AF will have stroke risk factors, making them eligible for an oral anticoagulant. Many will have concomitant cardiovascular disease (such as hypertension, valvular heart disease or heart failure) making them eligible for further investigation or treatment. Equally, in those with AF who are at low risk of stroke (and therefore do not qualify for oral anticoagulation), surveillance for increasing stroke risk is advisable.

Thus, the early diagnosis of AF, before the manifestation of the first complication, remains a major public health challenge. Screening for AF in the community has been proposed as an approach to optimise early AF detection.^4^ Previous studies have shown that the risk of AF (often asymptomatic) increases with age.^5^ Opportunistic screening is cost-effective in patients aged 65 years or over, and among individuals aged 75–76 years old undergoing a 2-week intermittent ECG screening.^6–8^ Nevertheless, there is no current recommendation for UK population-wide systematic screening.^9^

Prediction models could contribute to AF screening by discriminating patients into risk categories, from which investigation intensity could be planned.^10^ However, models based solely on analysis of investigations may not apply in the community setting—for example, routine ECGs are not always available.^11^

To date, several multivariable prediction models have been created or tested for prediction of incident AF in the community. The earliest models were derived from structured follow-up of prospective cohorts, including Framingham Heart Study score for Atrial Fibrillation and CHARGE-AF (Cohorts for Heart and Ageing Research in Genomic Epidemiology for Atrial Fibrillation).^12 13^ The proliferation of electronic health records (EHRs) has led to the development of several models from local registries, including Maccabi Healthcare Services and C_2_HEST (Coronary artery disease/chronic obstructive pulmonary disease, Hypertension, Elderly, Systolic heart failure, Thyroid disease).^14 15^ Structured EHRs offer larger sample sizes to assess more candidate variables and derive more generalisable models.

A systematic review found that the models derived from prospective cohorts had been more frequently externally validated. CHARGE-AF was the only model that showed significant overall discrimination in meta-analysis but its transportability to EHRs is still being investigated.^16 17^ Each model to date is, however, limited by one or more of their use of small, geographically remote or historical datasets, lack of temporal information, crude risk modelling with consequent suboptimal model performance and/or predictor variables not readily available in primary care.^18^ None has yet reached widespread clinical practice.

Machine learning is a data-driven approach that can identify non-linear associations and complex interactions between variables without the need to specify these relationships *a priori*.^19^ A recent study applying this methodology to a nationwide UK dataset produced a model with a greater discriminative capability than CHARGE-AF (area under receiver operating characteristic (AUC) 0.827 vs 0.725) in EHR.^19^

Artificial intelligence (AI) has several desirable features for prediction modelling from EHRs. It facilitates the use of vast quantities of event data and associated temporal information, handles many predictors with automatic variable selection techniques, accommodates non-linearities and interactions among variables, and enables a live learning approach (whereby the prediction model is automatically updated). A range of AI techniques have been applied to EHR data and have demonstrated better prediction power over traditional statistical approaches.^20^ Furthermore deep learning, a subfield of machine learning, can learn complex patterns from data to characterise higher level correlations among clinical events.^21^ Accordingly, it may derive robust patient representations from raw EHR data for prediction modelling without the need for manual, expert-dependent feature engineering like classic machine learning techniques, which places a limit on scalability and generalisability.^22^

Using AI to develop a predictive algorithm from routinely collected primary care EHRs could offer several advantages:

A model could predict the risk that a person will develop new-onset AF, and how that evolves over time, whereas current prediction models only provide a fixed prediction horizon. This would allow phenotype-specific and temporal-specific screening which could make screening more efficacious and cost-effective.A model created from routinely collected EHRs could be more smoothly translated into clinical practice by being embedded into existing clinical EHRs.The predictive magnitude of variables for the development of AF may identify novel risk markers for AF, which could then be studied for causality.

### Research aim

The aims of the Future Innovations in Novel Detection of Atrial Fibrillation (FIND-AF) study are to:

Develop a deep learning model for predicting the risk, *and evolution of the risk,* of new-onset AF in primary care.Identify and quantify the magnitude of risk markers of new AF among routinely collected primary care data.Externally validate the model in a geographically distinct dataset to assess generalisability.

The extracted datasets, including linked data, comprise all patients for the period between 2 January 1998 and 30 November 2018 from the snapshot of CPRD-GOLD and CPRD-AURUM provided in October 2019. Over this study period, the CPRD-GOLD dataset comprises approximately 4.5 million patients eligible for data linkage at an up-to-standard practice, with over 200 000 patients having a record of AF. The CPRD-AURUM dataset comprises approximately 18 million patients eligible for data linkage, with almost 800 000 patients having a record of AF. A sample of 245 general practices will be randomly selected from 800 general practices in CPRD-AURUM to approximately match the size of CPRD-GOLD.

### Patient and public involvement

Patients and the public were not involved in the design of this research. However, a Scientific Advisory Board, including representatives from the Arrhythmia Alliance, National Institute for Health and Care Excellence AF guideline committee lay members (last updated 04 January 2020) and EHR software providers, has been created to provide expert context advice on the research, the dissemination of results and advise on the translation of the findings of this study into clinical practice.

### Inclusion and exclusion criteria

The study population will comprise all available patients in CPRD-GOLD and CPRD-AURUM eligible for data linkage and with at least 1-year follow-up in the period between 2 January 1998 and 30 November 2018. Patients will be excluded if they were 18 years of age or under at the date of the first registration in CPRD, diagnosed with AF or atrial flutter (AFl) before 1 January 1998, registered for less than 1 year in CPRD or ineligible for data linkage.

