### Outcome ascertainment

The outcome of interest is first diagnosed AF or AFl after baseline (1 January 2009). We have included AFl as an outcome since it has similar clinical relevance, including thromboembolic risk and anticoagulation guidelines, as AF.^1^ These will be identified using Read codes and SNOMED CT in CPRD datasets. For HES APC events and underlying cause of death variable in the ONS Death Registration data file, the 10th revision of the International Statistical Classification of Diseases and Related Health Problems (ICD-10) codes will be used. Misclassified data can lead to systematic prediction errors and accuracy of data may vary over time.^29^ CPRD has converted older ICD codes to the newer version, increasing confidence in their validity. Nonetheless, to verify data accuracy, we will check the data accuracy by year and include the year of AF diagnosis in the prediction models to assess their impact.

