### Sample size

To develop a prognostic prediction model, the required sample size may be determined by three criteria suggested by Riley *et al*.^30^ For example, suppose a maximum of 200 parameters will be included in the prediction model and the Cox-Snell generalised R^2^ is assumed to be 0.01. A total of 377 996 patients will be required to meet Riley’s criterion (1) with global shrinkage factor of 0.95; this sample size also ensures a small absolute difference (Δ<0.05) in the apparent and adjusted Nagelkerke R^2^ (Riley’s criterion (2)) and ensures precise estimate of overall risk with a margin of error <0.001 (Riley’s criterion (3)). According to the Quality and Outcomes Framework, the prevalence of AF in England is 1.7%.^31 32^ Given an AF prevalence of 1.7%, only 6425 patients will be expected to develop AF from 377 996 patients. Therefore, the number of patients in the CPRD dataset with AF will provide sufficient statistical power to develop and validate a deep learning prediction algorithm with the predefined precision and accuracy.

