### Missing data

Missing data are expected in EHR data, and will be handled using multiple imputations according to the approaches suggested by Carpenter and Kenward, and depending on the amount of missing data.^33^ It is likely there will be misclassification of baseline characteristics, such as smoking status, cholesterol, blood pressure and weight that change over time. To account for this, we will define baseline information using only measures recorded within the last year. We will then use measures taken within the last 2–5 years and in the year after baseline as parameters in the chained imputation equations used to impute baseline covariates with ≤40% missingness. In addition, median imputation, a common approach to deal with missing values in machine learning algorithms, will be used to test the model robustness.^34^

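### Eligibility is tied to any 1 year of follow-up in 1998–2018, not to registration on the 1 January 2009 baseline, so the rule as written admits people not under general-practice observation at time zero

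*Protocol article*

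**What the plan says.** Inclusion and exclusion criteria takes all linkage-eligible patients in both databases "with at least 1-year follow-up in the period between 2 January 1998 and 30 November 2018". On age, it excludes anyone who was "18 years of age or under at the date of the first registration in CPRD". On prior disease, it excludes people "diagnosed with AF or atrial flutter (AFl) before 1 January 1998". On length of record and linkage, it excludes those "registered for less than 1 year in CPRD or ineligible for data linkage". Every time anchor in that section is the 1998–2018 window, the start of 1998, or first registration.

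Outcome ascertainment then fixes one calendar date for everybody: "The outcome of interest is first diagnosed AF or AFl after baseline (1 January 2009". AF is found from general-practice codes, linked hospital admissions (HES) and the underlying cause of death (ONS). Under Missing data, "we will define baseline information using only measures recorded within the last year". Older measures and those from the year after baseline serve only to impute these values.

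Development and external validation of model treats the outcome as binary, with risk possibly predicted from 1 month to 10 years. It lists a softmax classifier, support vector machine, random forest, naïve Bayes and a Cox model. The only patient counts are for the source data: "Over this study period, the CPRD-GOLD dataset comprises approximately 4.5 million patients eligible for data linkage at an up-to-standard practice", with a similar statement for AURUM.

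**The concern.** A prediction model needs a time zero at which each person is under observation, free of the outcome, and has a record from which predictors can be read. Here time zero is 1 January 2009, but the entry rule does not refer to it. Two kinds of people meet every stated criterion without a current general-practice record on that date: those who left or died before 2009, and those who registered after it.

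For the first group, general-practice AF is not observed at any time after baseline. For the second, it is not observed until they join. Neither group has general-practice measures from the year before baseline. Some classifiers must nevertheless assign each person a class. If the default is no AF, average risk is diluted, and a flexible model could learn to read a sparse record as low risk. AURUM uses the same criteria, so the same artefact could be present in the external validation.

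**Working it through.** **1. The plan's own figure.** Sample size uses "suppose a maximum of 200 parameters will be included in the prediction model", a Cox-Snell R² of 0.01 and a shrinkage factor of 0.95. The first criterion is n = P / [(S − 1) ln(1 − R²/S)] = 200 / [(−0.05) × ln(1 − 0.01/0.95)] = 377 996.5, which reproduces the stated 377 996. Expected events are 377 996 × 0.017 ≈ 6425, also as stated. The sample size is correct and this point does not depend on it.

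**2. The window against the baseline.** From 2 January 1998 to 30 November 2018 is W = 20.91 years. Of these, B = 11.00 years (53%) lie before 1 January 2009 and 9.91 years after.

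**3. Two patients against the stated rules.**

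| | Registered 1999–2003 | First registered 2014 |
|---|---|---|
| At least 1 year of follow-up in the window | yes | yes (if they stay 1 year) |
| Caught by a stated exclusion (adult at entry, linkable, no AF before 1998) | no | no |
| Registered on 1 January 2009 | no | no |
| General-practice measures in the year before baseline | none | none |
| General-practice AF observed after baseline | never | from 2014 only |

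**4. Illustration of size.** The documents give no turnover figure. Assume a stable list, exponential registration spells and yearly turnover r between 4% and 10%. Among people with at least 1 year in the window:

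- eligible, per person on the list: e^(−r) × [1 + r(W − 1)]
- of these, registered at baseline: e^(−r) × (1 + r)
- share registered at baseline: (1 + r) / (1 + 19.91r)
- share that left earlier: r(B − 1) / (1 + 19.91r)
- share that joined later: r(W − B − 1) / (1 + 19.91r)

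| r | registered at baseline | left before | joined after |
|---|---|---|---|
| 4% | 1.04/1.796 = 58% | 0.400/1.796 = 22% | 0.356/1.796 = 20% |
| 10% | 1.10/2.991 = 37% | 1.000/2.991 = 33% | 0.891/2.991 = 30% |

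A simulation of the same model with mean spells of 5, 10, 20 and 40 years gave 24%, 37%, 53% and 68% registered at baseline. The formula agrees (r = 0.05: 1.05/1.996 = 53%).

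**5. Size after the fix.** Requiring a full prior year of registration as well gives 1/(1 + 19.91r), or 56%–33%. Applied to the 4.5 million GOLD patients, the low end is 0.334 × 4.5 million ≈ 1.5 million. This is approximate, because 4.5 million is a source count taken before the age, AF and 1-year criteria. The break-even is 377 996 / 4.5 million = 8.4%, or 10.5% if the 80% training sample alone must meet the requirement (377 996 / 0.8 = 472 495).

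**The case against.** The best reply is that the 1998–2018 dates describe the data extraction, with 1998–2008 meant as look-back and 2009–2018 as outcome period, and that a condensed article leaves a registered-at-baseline filter to the full protocol. The imputation plan supports this as the intention. It imputes only covariates with at most 40% missing, and on the illustrative shares 42%–63% of the cohort would lack last-year measures altogether. That is fair evidence of intent. But the article is not silent: the dates stand in the section that defines the study population, with explicit exclusions, and those rules do not fit the stated baseline.

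Four limits on the harm do stand:

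- **Linked outcomes.** HES and ONS data may capture some AF outside registration. A reader might infer that early leavers are AF-free by construction, or that short-horizon outcomes of late joiners cannot be observed at all. The documents do not support either, since they do not say whether linked records outside registration are used.
- **Labelling.** No section says absent patients are counted as non-cases, and the Cox model would simply drop those with no time at risk. The bias is conditional on the labelling rule.
- **Predictors.** The deep learning models take the longitudinal event history as well as last-year measures, so an early leaver's record is not empty.
- **Double entry.** A reader might also infer that people who move between a GOLD and an AURUM practice are counted twice. Practices that contributed to both have been removed from the GOLD cohort. The article gives no information on individual movers, so this is not part of the point.

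**Conclusion.** The point holds on the text. The inclusion rule and the baseline do not fit together, and as written the cohort includes people with no current general-practice record at time zero. This concerns the definition of the prediction target and goes beyond omitted detail.

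The size cannot be derived from the documents. The 58%–37% registered at baseline rests wholly on assumed turnover of 4%–10%, a stable list and exponential spells. It shows only that the affected share could be large.

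The direction of bias (predicted risk too low, discrimination possibly inflated) applies if absent patients are labelled AF-free in the binary classifiers. It is tempting to turn the shares into a multiplier on predicted risk, but that would need both the true share and the labelling rule, and the article gives neither. Nor is the study underpowered: the sample-size figure reproduces and the margin is wide.

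**What to change.** Restate eligibility relative to baseline: alive, currently registered at an up-to-standard practice with at least 1 year of prior registration, and free of AF/AFl, all on 1 January 2009. The last condition also replaces the AF exclusion now dated to 1998.

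If later registrants are wanted, give each patient an index date equal to the later of 1 January 2009 and 1 year after registration. Include only those still alive, registered and AF/AFl-free on that date, and measure predictors and every horizon from it. The condition of still being registered is essential. Without it, someone who left in 2003 would receive 1 January 2009 as index date and stay in.

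Apply the same rule in GOLD and AURUM, and report the resulting cohort and AF counts beside the source counts in Data sources and permissions.

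The cost is a change of wording and a filter on data already extracted. The downside is a smaller cohort, which on the illustrative shares stays well above 377 996.

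### The AF exclusion stops at 1 January 1998 but baseline is 1 January 2009, so patients first diagnosed in the 11 years between stay in a cohort meant to predict new-onset AF

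*Protocol article*

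**What the plan says.** The Inclusion and exclusion criteria admit patients eligible for linkage "with at least 1-year follow-up in the period between 2 January 1998 and 30 November 2018". They exclude those "diagnosed with AF or atrial flutter (AFl) before 1 January 1998". The remaining exclusions concern age at first registration, less than a year of registration, and ineligibility for linkage.

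The next section, Outcome ascertainment, sets the outcome and the time origin together: "The outcome of interest is first diagnosed AF or AFl after baseline (1 January 2009". This is the only place where the 2009 date appears.

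Under Data sources and permissions, the extracts "comprise all patients for the period between 2 January 1998 and 30 November 2018". Over that whole window the article reports CPRD-GOLD "with over 200 000 patients having a record of AF" and CPRD-AURUM "with almost 800 000 patients having a record of AF".

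The Research aim is to predict the risk "of new-onset AF in primary care". The Predictor variables section opens the candidate list to every recorded condition, hospital event and medication. It does not set aside earlier AF codes or AF treatment.

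**The concern.** A model of new-onset disease needs a cohort free of that disease when the clock starts. Here the disease exclusion and the clock are 11 years apart. A patient first coded with AF in 2004 passes every listed exclusion and is in the cohort on 1 January 2009 with known AF.

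That patient cannot have a first diagnosis after baseline. If the outcome wording is followed, the patient is recorded as a non-event despite already having the disease. A group with the AF risk profile, and with AF codes and AF treatment available as inputs, is then labelled as not developing AF. This can bias the estimated risk for similar patients, disturb calibration where earlier AF is most common, and give misleading weights to the markers that the second research aim sets out to quantify. If programmers instead take the first AF record seen after 2009 as the outcome, the same patient becomes a false incident case.

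External validation offers no protection, because the criteria apply to CPRD-GOLD and CPRD-AURUM alike.

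**Working it through.** **1. The plan's own sample-size figure.** Inputs from the Sample size section: 200 parameters, shrinkage 0.95, Cox-Snell R² 0.01, AF proportion 1.7%.

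- n = p / ((S − 1) × ln(1 − R²/S)) = 200 / ((0.95 − 1) × ln(1 − 0.01/0.95)) = 377,996 (stated: 377 996).
- Expected cases = 0.017 × 377,996 = 6425.9 (stated: 6425).

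Both reproduce. No calendar date enters either formula, so the date conflict leaves them unchanged.

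**2. The dates side by side.**

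| Interval | Length |
|---|---|
| Exclusion limit (1 Jan 1998) to baseline (1 Jan 2009) | 4018 days = 11.0 years |
| Start of window (2 Jan 1998) to baseline | 4017 days |
| Baseline to end of window (30 Nov 2018) | 3620 days = 9.91 years |
| Whole window | 7637 days = 20.9 years |

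The share of the window before baseline is 4017 / 7637 = 52.6%.

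**3. Does another rule close the gap?** The four exclusions were checked against a patient first diagnosed in 2004, registered as an adult for several years and eligible for linkage. None applies. No other section adds an exclusion.

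**4. How many patients?** The article gives AF counts for the whole window, with no breakdown by year, so a range has to be assumed. The upper value of 53% is the calendar share in step 2, that is, first diagnoses spread evenly over the window. The lower value of 20% is an arbitrary low case.

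- CPRD-GOLD, low: 0.20 × 200,000 = 40,000 before baseline, leaving 160,000.
- CPRD-GOLD, high: 0.53 × 200,000 = 106,000 before baseline, leaving 94,000.

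The 40,000 to 106,000 must be reduced by those who had died or left by 2009, which the article does not allow us to estimate.

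**5. Which date is wrong?** The 1998 limit fits a cohort entering at the start of the data window on 2 January 1998. A 2009 baseline leaves 9.91 years, just short of the 10-year horizon listed under Development and external validation of model. Both facts suggest that 2009 could be the misstatement, but neither settles it.

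**The case against.** The strongest reply is that the outcome is a first diagnosis after baseline and the aim speaks of new onset, so earlier AF is excluded by implication. This stands in part. The word first does stop a patient diagnosed in 2004 and re-coded in 2010 from counting as a case. It does not remove that patient from the study population, which is all available patients less the listed exclusions.

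A second reply is that 2009 may be the slip. If entry in 1998 is intended, the exclusion date already fits and no one is wrongly retained on this account. That is possible, and it is why the point is a conflict between two sections rather than a proven retention of prevalent cases. One of the sections must still change.

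Three stronger readings are tempting and are not supported.

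- A reader might infer that prevalent patients are counted as new cases and that discrimination is therefore inflated. That requires ignoring the word first in the outcome definition. Any figure for the change in AUC would also need the retained share and the score distributions, which the article does not give.
- A reader might infer that more than half of the AF patients, over 100,000, are affected. That is calendar arithmetic under even accrual, at the top of an assumed range and before losses to 2009.
- A reader might see the same fault in the age rule: "Patients will be excluded if they were 18 years of age or under at the date of the first registration in CPRD". That rule restricts the population and contradicts nothing. The database dates from 1987. If registration means entry to it, those excluded were at most about 18 + (2009 − 1987) = 40 at baseline, and the Introduction notes that AF risk rises with age.

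**Conclusion.** The point holds as a conflict between two adjacent sections that makes the cohort wrong as written. Patients first diagnosed from 1 January 1998 to 31 December 2008 remain in a cohort meant to be at risk of new-onset AF. That follows from the two dates alone and needs no assumption.

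The likely form of the error is prevalent AF among the non-events. False incident cases arise only if the outcome is programmed against its own wording. The direction and size of the effect on calibration, discrimination and marker weights cannot be stated from the document. The 40,000 to 106,000 patients in CPRD-GOLD rest on the assumed 20% to 53% and on taking 200,000 as the total. The sample-size calculation is not affected.

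**What to change.** Use one entry date in both Inclusion and exclusion criteria and Outcome ascertainment. Exclude anyone with an AF or flutter record before that date in CPRD or linked HES, in CPRD-GOLD and CPRD-AURUM alike.

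- If 1 January 2009 is the intended baseline, change the exclusion limit from 1 January 1998 to 1 January 2009.
- If entry in 1998 is intended, correct the baseline in Outcome ascertainment.

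The cost is a change of wording and one cohort filter. With a 2009 baseline, the cohort and the AF count become somewhat smaller. Even the high assumption in CPRD-GOLD leaves about 94,000 patients with a later first diagnosis, before the other exclusions. That is likely to stay far above the 6425 cases in the sample-size section.
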